#### ARF diagnostic criteria

2.6.3

The 2015 modified Jones criteria (13) for high-risk populations will be used. The diagnosis of ARF is made if two major or one major and two minor criteria are met along with the evidence of streptococcal infection. If ARF is thought to be a recurrent episode, three minor criteria can be used to make the diagnosis. Major criteria include presence of carditis, mono- or polyarthritis, polyarthralgia, chorea, erythema marginatum, and subcutaneous nodules. Minor criteria include monoarthralgia, fever ≥38.0 °C, elevated inflammatory markers: ESR ≥30 mm/h and/or CRP ≥3.0 mg/dL, or prolonged PR interval on ECG. Prolonged PR interval is counted as a minor criterion only if carditis is not being used as a major criterion. There must be evidence of preceding group A streptococcal infection which is required for all except isolated chorea or indolent carditis. Antistreptolysin O Titer (ASOT) testing is provided to all facilities by the PRIMA study and will be the most common GAS antibody test used, though anti-DNase B titer, positive throat culture for GAS, and positive rapid antigen detection testing for GAS can also be used.

Carditis may be clinical or subclinical. Subclinical carditis is defined by Doppler echocardiographic evidence of pathological mitral or aortic regurgitation and morphologic changes as detailed in the 2023 World Heart Federation guidelines for the echocardiographic diagnosis of RHD (14). Echocardiographic assessments are performed using standardized imaging checklists which specifically include the criteria for pathological regurgitation and morphologic change. Echocardiograms are all uploaded for central review by cardiologists to support diagnostic consistency and fidelity. Kathmandu-based cardiologists serve as the final interpretive authority for echocardiographic findings, consistent with specialist referral practice within Nepal's health system. All clinics are equipped with a cardiac ultrasound machine.

Cases in which diagnostic criteria are not clearly met are reviewed by a study cardiologist, and children may be classified as suspected or probable ARF when appropriate. Diagnostic classification may be updated over time as additional clinical, laboratory, or echocardiographic information becomes available during follow-up, which reflects real-world practice.

Procedures related to recruitment of controls and biomarker analysis (blood sample collection) as part of the larger multi-national PRIMA study will be collected, however they are not the focus of this implementation analysis and thus are not described.

### Data collection and management

2.7

Clinical data from initial consultation will be collected using standardized electronic case report forms in REDCap, which comprises the registry. Echocardiographic images will be exported from the ultrasound machine to Tricefy, an online cloud-based repository, and linked by unique study IDs. Patients who have positive echocardiograms will be followed up at their local health facility monthly per clinic protocols, and at 3, 6, and 12 months they will be followed up per study protocols using a REDCap form. Echocardiographic quality will be monitored by cardiologists, and constructive feedback will be provided to performing physicians at the recruiting facilities as needed. Program delivery and data quality will be monitored through periodic review of REDCap registry completeness and monthly quality check-ins will be conducted by the central KIOCH team.

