#### Clinical evaluation workflow

2.6.2

ARF cases will be diagnosed if children meet 2015 modified Jones criteria (13) for high-risk populations. Nurses and physicians at participating facilities will confirm the diagnosis through laboratory tests, physical examination, and echocardiography. ARF diagnostic criteria included in SOPs and REDCap registry forms guide providers in confirming diagnostic criteria for enrollment.

Cases that are determined to be likely ARF are entered into the registry and their echocardiograms are uploaded for review by cardiologists. There are several participating cardiologists at tertiary care facilities in the capital city of Kathmandu who will provide diagnostic support and clinical advice as requested by study clinicians. Recruitment and follow-up will occur continuously, with structured follow-up visits scheduled at 3, 6, and 12 months post-enrollment for each ARF patient. Children requiring penicillin prophylaxis will be reviewed clinically in accordance with national follow-up guidelines. Follow-up will occur at the closest participating facility to the child's residence.

At each participating site, implementation is led by a designated clinical team comprising a physician, staff nurse, and laboratory technician. This team is responsible for application of ARF diagnostic criteria, echocardiographic assessment, registry documentation, and coordination of follow-up care.

Training was held by KIOCH in November 2025 during which SOPs for recruitment, ARF diagnostic criteria, and echocardiography protocols were reviewed with all providers and distributed. All facilities are expected to adhere to centrally defined SOPs and any deviations or contextual constraints will be documented in detail and reviewed during monthly monitoring and quality assurance meetings with the central KIOCH team.

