#### Data sources

2.9.1

Data sources include facility clinical records, REDCap clinical data, provider and hospital superintendent surveys, and monthly monitoring reports with site-based study leads.

Facility clinical records: We will examine the routine paper-based clinical forms that exist in the facilities. We will examine background data on participants, as well as monthly records for participants who are positive for ARF. At the end of the program, researchers will hand search clinical forms to extract relevant data.

REDCap clinical data: Three types of REDCap clinical data will be used for this study.
When a suspected case is referred to a participating facility, the study encounter and suspected diagnosis will be recorded in REDCap.If the case screens positive for ARF, their echocardiogram will be reviewed by a Kathmandu-based cardiologist who will report their echocardiographic findings in REDCap.Per study protocol, at three study points (3, 6, and 12 months) patients diagnosed with ARF will be monitored for progress. These visits will be conducted using REDCap forms.Provider surveys: Surveys will be distributed at 12 months to all providers (one doctor and one nurse at each facility). Surveys will consist of a mix of multiple choice, Likert-scale and free text questions. These will be conducted in a mix of English and Nepali and will be conducted through Google forms.

Hospital superintendent surveys: Surveys will be distributed at 12 months to the superintendent in charge of each facility enrolled in this study. Surveys will consist of a mix of multiple choice, Likert-scale and free text questions. These will be conducted in a mix of English and Nepali and will be conducted through Google forms.

Monthly monitoring reports: Once a month, a central researcher from KIOCH will hold a “monthly check-in” with each of the 11 site-based study leads. These free-form discussions will cover barriers and solutions encountered over the past month, as well as number of cases, perceptions of case mix, and any questions that have arisen. These check-ins will not have audio recording but the KIOCH researcher will take detailed notes.

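### The 3-, 6- and 12-month study visits are assigned to ARF patients in two sections and to echo-positive patients in a third, so it is not settled over which children follow-up completion is computed

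*Protocol article*

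**What the plan says.** Three sections of the protocol article say who attends the study visits.

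- Section 2.6.2 (Clinical evaluation workflow) describes continuous recruitment, "with structured follow-up visits scheduled at 3, 6, and 12 months post-enrollment for each ARF patient". It sets no echocardiographic condition.
- Section 2.9.1 (Data sources) says that "at three study points (3, 6, and 12 months) patients diagnosed with ARF will be monitored for progress", and adds: "These visits will be conducted using REDCap forms". Again there is no echocardiographic condition.
- Section 2.7 (Data collection and management) starts from a different group: "Patients who have positive echocardiograms will be followed up at their local health facility monthly per clinic protocols". The sentence goes on "and at 3, 6, and 12 months they will be followed up per study protocols using a REDCap form", where the pronoun refers back to the echo-positive patients.

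A third class of child appears in Section 2.6.3 (ARF diagnostic criteria). Where the criteria are not clearly met, "children may be classified as suspected or probable ARF when appropriate", and the classification may change later. Table 1 counts suspected as well as confirmed cases among enrolled children. No section says in terms whether these children are due study visits.

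Completion of the three visits is listed among the exploratory care-process indicators in the last row of Table 1, with patient and facility as the unit. It is mentioned again in Section 2.10 (Analysis) and in the Abstract. None of these places states its denominator.

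**The concern.** A completion proportion has meaning only against the set of children who were due a visit. The article names that set in two ways, for the same time points and the same data capture. This is a different matter from a detail left to a fuller document: two statements are given, and they do not match.

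Two things follow. The same attendance data can give different completion figures, depending on which statement the analyst takes as the denominator. And if facilities schedule different children, a visit that was never arranged may be counted as missed. Section 2.10 reports results facility by facility and by facility type, and the Discussion expects geography and socioeconomic constraints to affect retention. A difference in scheduling practice would be mixed into exactly that interpretation.

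**Working it through.** The article gives no sample size, expected case count, echo-positive share or follow-up rate, so there is no figure to reproduce. The check is a comparison of the text.

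**Step 1: are the two groups the same under the protocol's own criteria?**

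- ARF without a positive echocardiogram is possible. Section 2.6.3 lists carditis as one of several major criteria, next to joint involvement, chorea and skin findings, and does not require it.
- A positive echocardiogram without ARF is possible. Section 2.5 says children at the facilities are screened for RHD as well as ARF, and Section 2.6.1 includes abbreviated echocardiography in schools.

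The groups therefore differ in both directions.

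**Step 2: which children does each section name for the study visits?**

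| Child | 2.6.2 (ARF patient) | 2.9.1 (diagnosed with ARF) | 2.7 (positive echo) |
|---|---|---|---|
| ARF, positive echo | named | named | named |
| ARF, normal echo | named | named | not named |
| Positive echo, no ARF | not named | not named | named |
| Suspected or probable, positive echo | unclear | unclear | named |
| Suspected or probable, normal echo | unclear | unclear | not named |

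Only the first row is settled by all three sections.

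**Step 3: what does this do to a completion figure?**

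Leave suspected and probable cases aside. Let A be the number of children with ARF and a positive echo, B with ARF and a normal echo, and C with a positive echo and no ARF.

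- Denominator under Sections 2.6.2 and 2.9.1: A + B.
- Denominator under Section 2.7: A + C.

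These are the same children only if B = 0 and C = 0. Suppose one facility schedules all ARF patients and another schedules only echo-positive children, that the same fraction r of scheduled children attends at both, and that completion is reported over all ARF patients. The first facility shows r(A + B)/(A + B) = r. The second shows rA/(A + B), which is lower whenever B > 0, although retention of scheduled children is identical. The factor A/(A + B) is the echo-positive share among ARF patients. The article does not give it, so the gap cannot be put in numbers.

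**The case against.** The strongest reply is that Section 2.7 does not say that only echo-positive patients are followed. Its distinct content is the monthly clinic follow-up, and for the study visits it points to study protocols. On that reading every child with ARF gets the study visits and echo-positive children also come monthly. This reconciles the sections for children with ARF. It does not settle echo-positive children without ARF, or suspected and probable cases, and Section 2.7 remains the data collection section's only statement of who is followed.

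It is also fair that no two stated denominators conflict, because none is stated. The ambiguity in the denominator is inferred from the differing visit groups. Sites work from distributed SOPs with training and monthly monitoring (Section 2.6.2), and those SOPs may already be consistent. The indicator is exploratory, Section 2.10 says the study is not designed for formal between-facility comparisons, and no success thresholds are set.

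Three stronger readings are tempting and are not supported:

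- A reader might infer that children without carditis have no visit form. Section 2.9.1 provides REDCap forms for the visits of all patients diagnosed with ARF, so this would need Section 2.7 to be exclusive and to override it.
- A reader might infer that suspected cases cannot be upgraded, which would make reclassification one-sided. Section 2.6.3 provides for review by a study cardiologist and allows reclassification on any later clinical, laboratory or echocardiographic information. Suspected cases may also fall under the wording of Section 2.6.2.
- A reader might infer a ceiling on completion, for example 1 − 0.30 = 70% down to 1 − 0.50 = 50% if 30% to 50% of ARF children had a normal echo. That share is an assumption with no source in the article, and the ceiling also needs every site to treat Section 2.7 as exclusive.

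**Conclusion.** The inconsistency stands. Sections 2.6.2 and 2.9.1 define the study-visit group by ARF, Section 2.7 defines it by a positive echocardiogram, and the protocol's own criteria make these different groups. The position of suspected and probable cases is open. Completion of the visits can therefore be computed over different sets of children, and facility figures may mix scheduling with retention.

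The consequence is limited. The indicator is descriptive and exploratory, and none of the primary outcomes (acceptability, feasibility, adoption) is defined by it. A reader might infer that feasibility is affected as well, since Section 2.10 measures it partly by the percentage of workflows completed. The article does not say that this percentage counts follow-up visits, so that link is not established.

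The conclusion assumes only that at least some enrolled children fall outside the first row of the table. No magnitude is claimed.

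**What to change.** Reconcile Sections 2.6.2, 2.7 and 2.9.1 into one statement of which children are due the 3-, 6- and 12-month study visits, and say whether suspected and probable cases are covered. Which children these are is a clinical decision for the sponsor.

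Then, for the analysis:

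- Define the denominator of follow-up completion at each time point as exactly the children due that visit under the statement.
- Have REDCap scheduling follow the statement, including after a child is reclassified. A schedule fixed at the enrolment classification would presuppose a rule and could miss children upgraded later.
- Report completion split by echo status and by diagnostic certainty (definite versus suspected or probable), so that a reader can see what each figure covers.

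The cost is a consistent sentence in three sections, a scheduling rule in REDCap and a minor re-briefing of sites. Recruitment began in February 2026 (Section 2.1), and a visit that was never scheduled cannot be recovered afterwards, so early clarification is worth more than late.

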### Outcome measures and data sources

2.8

Evaluation of the ARF case-finding program will use Proctor's taxonomy of implementation outcomes (8) with a primary focus on acceptability, feasibility, and adoption during early program delivery across diverse health system contexts in Nepal. Implementation outcomes are summarized in Table 1. Definitions and examples of Proctor's taxonomy outcomes are provided in Supplementary Table 1. These outcomes will be assessed primarily at the facility level to reflect integration of the standardized workflow into routine clinical practice. Implementation outcomes will be evaluated from April 2026 to April 2027, following a two-month run-in period.

**Table 1 T1:** Implementation outcomes evaluated in this study protocol, organized according to Proctor's taxonomy (8) with corresponding units of analysis, key evaluation questions, data elements, and data sources. The final row describes exploratory care-process indicators assessed at the patient and facility level during the first 12 months of program delivery; these are not Proctor outcomes and are not intended to evaluate clinical effectiveness. ARF, acute rheumatic fever; FCHV, Female Community Health Volunteer; QA, quality assurance; REDCap, Research Electronic Data Capture; SOP, standard operating procedure.

Proctor outcome(s)	Unit of analysis	Key questions addressed	Data elements	Data sources
Penetration	Facility/catchment	Are children with symptoms suggestive of ARF being identified and evaluated within routine care?	Number of children evaluated for ARF per site Number and characteristics of children enrolled with suspected or confirmed ARF Distribution by age, sex, distance to facility, and referral source	REDCap clinical data Facility clinical records
Acceptability	Provider/facility	Is the program acceptable to the people delivering it? Do providers and hospital administrators think it is adding to their workload.	Do providers agree with the program? Do providers think it is adding to the workload? Provider-reported perceived usefulness and acceptability	Provider/FCHV structured surveys Hospital superintendent structured surveys
Adoption	Facility/provider	Have participating facilities initiated and operationalized the standardized ARF case-finding and registry workflow?	Number and proportion of facilities initiating the full workflow Number and cadre of providers participating	Facility clinical records Provider structured surveys
Feasibility	Facility/provider	Can the standardized workflow be delivered within routine inpatient and outpatient care?	Reported workflow barriers Time burden estimates Documentation of contextual constraints	Monthly monitoring reports Provider structured surveys
Fidelity	Facility/provider	Are ARF diagnostic and registry procedures implemented according to centrally defined SOPs?	Proportion of evaluations meeting Jones criteria documentation standards Echocardiography completeness and image adequacy Registry completeness Frequency and nature of protocol deviations	REDCap clinical data Monthly monitoring reports
Sustainability	Facility	Is the program still operational with sustained adherence at 12 months?	Continued ARF case enrollment activity Continued registry use Ongoing participation in QA processes Sustained workflow adherence	REDCap clinical data Monthly monitoring reports
—	Patient/Facility	How is the standardized workflow functioning clinically during early implementation?	Number and proportion of ARF diagnoses among evaluated children Diagnostic concordance with central cardiologist review Time from symptom onset to diagnosis Time from diagnosis to initiation of prophylaxis Follow-up completion at 3, 6, and 12 months	REDCap clinical data Facility clinical records

Exploratory care-process indicators will be assessed at the patient level and are intended to characterize whether the intervention may function to improve ARF care in the absence of pre-implementation comparator data. These include the number and proportion of ARF diagnoses among evaluated children, accuracy and timeliness of diagnosis, linkage to follow-up care, and follow-up completion over time. These measures are descriptive and are not intended to evaluate long-term clinical effectiveness.

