**Methods:**

This protocol describes implementation of a standardized ARF case-finding program and integrated clinical and echocardiographic registry across 11 district and referral hospitals in Nepal. The program is delivered through the PRIMA Network in partnership with the Kathmandu Institute of Child Health (KIOCH), embedded within existing PEN-Plus chronic disease infrastructure at district-level facilities. Case-finding is integrated into routine care using the 2015 modified Jones criteria, standardized echocardiography protocols, centralized training, and REDCap registry-based follow-up. Implementation outcomes are evaluated using Proctor's taxonomy, focusing on acceptability, feasibility, and adoption of the program within routine care, rather than on clinical detection rates or RHD outcomes. Contextual determinants are examined using the Consolidated Framework for Implementation Research (CFIR). Care-process indicators including diagnostic patterns and follow-up completion are summarized descriptively over the first 12 months of program delivery.

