### Study design

2.1

This is a protocol for a prospective, pragmatic, multi-site implementation study conducted across six district and five referral hospitals in Nepal. This observational study evaluates early implementation of a standardized ARF case-finding and registry program embedded within routine inpatient and outpatient care. The primary unit of analysis is the participating facility, reflecting integration of the standardized workflow across Nepal's diverse geographic and socioeconomic health system contexts. Implementation outcomes will be evaluated over the first 12 months of program delivery after a two-month run-in period (April 2026-April 2027) using a mixed-methods, registry-based approach. The study is conducted within the broader PRIMA research platform but focuses specifically on implementation of the ARF case-finding and registry workflow.

Recruitment activities began in February 2026 and will continue on a rolling basis across participating facilities.

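### Within the April 2026 to April 2027 window, 12-month follow-up completion can be observed only for the earliest-enrolled children, and the 3- and 6-month visits are not yet due for later enrolees

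*Protocol article*

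**What the plan says.** Four statements in the protocol article bear on this.

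- **Indicator.** The last row of Table 1 (section 2.8) names "Follow-up completion at 3, 6, and 12 months". The caption describes that row as "exploratory care-process indicators assessed at the patient and facility level during the first 12 months of program delivery".
- **Window.** The Abstract (Methods) says "Care-process indicators including diagnostic patterns and follow-up completion are summarized descriptively over the first 12 months of program delivery". Section 2.8 gives the dates: "Implementation outcomes will be evaluated from April 2026 to April 2027, following a two-month run-in period". Section 2.1 gives the same dates for the first 12 months of delivery.
- **Enrolment.** Section 2.1: "Recruitment activities began in February 2026 and will continue on a rolling basis across participating facilities". No end date is given. Section 2.10 uses continued case enrolment at 12 months as a sustainability measure, so enrolment is expected to run to the close.
- **Visit clock.** Section 2.6.2 has "structured follow-up visits scheduled at 3, 6, and 12 months post-enrollment for each ARF patient".

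Section 2.10 says that follow-up completion is summarised descriptively at the patient level. The article does not state the denominator at each visit, a later data cut for this indicator, or whether children enrolled in the run-in are counted.

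**The concern.** The window is fixed by the calendar, while each visit is fixed by the child's enrolment date. When the window is no longer than the longest visit interval, a child who enrols after it opens has a 12-month visit due after it closes. One of the three named time points is then almost empty at the planned report. What it does contain comes from children recruited while sites were starting up, who may not represent later practice.

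The 3- and 6-month visits are affected to a lesser degree: children enrolled in the last three or six months have not reached them. If completion were divided by all enrolled children, a visit not yet due would be counted as missed, and a program with full attendance would appear to lose patients. Section 2.10 reports results by facility and by facility type, so sites that enrol later would look worse because of the calendar alone. Section 3 already warns that geography and socioeconomic constraints may affect retention independently of program performance; a calendar artefact could not be told apart from them.

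**Working it through.** The plan states no sample size, accrual rate or expected completion figure, so there is nothing of its own to reproduce. The check is date arithmetic.

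**Inputs.** Recruitment starts in February 2026 (2.1). The window runs from April 2026 to April 2027 after a two-month run-in (2.1, 2.8). Visits are due *v* = 3, 6 and 12 months after enrolment (2.6.2). Day of month is not given, so 1 February and 1 April 2026 are taken as starts, and 1 April or 30 April 2027 as the close. Accrual shape is an assumption.

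**Step 1: individual dates.** A child enrolled on 1 April 2026 is due the 12-month visit on 1 April 2027, the close itself on the earlier reading. Later enrolees are due after that. A child enrolled in the run-in is due between February and April 2027, inside the window.

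**Step 2: share of children whose visit is due by the close.** With accrual over *T* months ending at the close:

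- uniform accrual: (*T* − *v*)/*T*, not below 0
- linear ramp-up from zero: ((*T* − *v*)/*T*)²
- linear decline to zero: 1 − (*v*/*T*)²

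| Children counted, close, accrual | T | 3 months | 6 months | 12 months |
|---|---|---|---|---|
| Window only, 1 April 2027, uniform | 12 | 9/12 = 75% | 6/12 = 50% | 0/12 = 0% |
| Window only, 30 April 2027, uniform | 13 | 10/13 = 77% | 7/13 = 54% | 1/13 = 8% |
| With run-in, 1 April 2027, uniform | 14 | 11/14 = 79% | 8/14 = 57% | 2/14 = 14% |
| With run-in, 30 April 2027, uniform | 15 | 12/15 = 80% | 9/15 = 60% | 3/15 = 20% |
| With run-in, 1 April 2027, ramp-up | 14 | (11/14)² = 62% | (8/14)² = 33% | (2/14)² = 2% |
| With run-in, 1 April 2027, decline | 14 | 1 − (3/14)² = 95% | 1 − (6/14)² = 82% | 1 − (12/14)² = 27% |

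Starting from the 14-month uniform case and changing the closing date or the accrual shape one at a time, the 12-month share runs from 2% to 27%. Combining the two favourable choices (decline and a 30 April close) gives 1 − (12/15)² = 36%, still a minority.

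**Step 3: meaning of these shares.** They are the fractions of enrolled children for whom the visit could have happened by the close. They equal the highest attainable completion rate only if all enrolled children are the denominator.

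**Step 4: effect of late enrolment, as an illustration.** Take a hypothetical facility that enrols uniformly over the last six months only. The shares due are (6 − 3)/6 = 50% at 3 months and 0% at 6 and 12 months, whatever its true retention.

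**The case against.** Several objections carry weight.

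- **The 12-month visit is not unobservable.** A reader might infer that nothing can be seen at month 12. The documents do not support that: recruitment began in February 2026, so run-in children reach month 12 inside the window, as do the earliest April 2026 enrolees if it closes at month end. Nor can that group be called a handful, since no enrolment numbers are given.
- **No denominator is stated.** A reader might infer that the 3- and 6-month figures will be biased downwards. That follows only if all enrolled children are the denominator. Dividing by visits already due is compatible with the text, and an article may leave such detail to a fuller document. This part of the point is therefore conditional.
- **The calendar dates are attached to implementation outcomes.** The Table 1 caption says the care-process row is not a set of Proctor outcomes, and section 2.9.1 places the hand search of paper forms at an undated end of the program. This softens the point only a little, because the Abstract and the caption both tie these indicators to the first 12 months of delivery.
- **No primary outcome is shown to depend on it.** Section 2.10 measures feasibility partly by the percentage of workflows completed in REDCap, and a reader might infer that follow-up visits are included. The article does not say so. The indicator is one of five elements in an exploratory row, there are no success thresholds, and formal between-facility comparison is ruled out.

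The mismatch between the stated window and the 12-month visit survives all of this. It is more than an omitted detail: an analysis plan that kept to the stated window could not supply the 12-month figure for most children under any accrual shape tried here.

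**Conclusion.** The point holds at moderate severity. Followed as written, the plan can report 12-month completion only for the earliest-enrolled children: 0% of those enrolled from 1 April 2026 to 1 April 2027, about 14% with the run-in counted under uniform accrual, and about 2% to 27% when accrual shape or closing date is varied singly. All of these rest on assumed accrual. That later enrolees cannot reach month 12 inside the window rests on the dates alone.

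The 3- and 6-month visits are truncated too, but whether the reported rates would be understated depends on a denominator the article leaves open. The documents do not support saying that month 12 cannot be observed at all, or that any primary outcome is compromised.

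**What to change.** In Table 1, section 2.8 and section 2.10:

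1. Define the denominator at each visit as the children whose visit (with any visit window) has fallen due by the data cut, and show the number not yet due separately, by facility.
2. State the data cut for this indicator and whether children enrolled in the run-in count.
3. Report 12-month completion from a later cut of the REDCap visit forms. For children enrolled up to April 2027 that means April 2028 plus any visit window. Alternatively, show it in the 12-month report only for the earliest-enrolled cohort, labelled as such.

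A retention curve (Kaplan-Meier) censored at the data cut is optional.

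The cost is wording and one later export; the visits are already scheduled, so none need be added. The drawback is that the full 12-month figure arrives about a year later. This Table 1 row also draws on facility clinical records, which section 2.9.1 says are hand-searched on paper. Confining the later cut to REDCap forms avoids repeating that search across 11 sites; if paper records are needed to confirm attendance, the cost is larger.
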